#### Enrollment

Patients with age above 40 who applied to family medicine units for any reason and screened within the scope of periodic health care for diabetes are eligible for the study. Guidelines determine that 40 is the age to start diabetes screening for people without having any risk factors [9, 10].

Around 3000 people over the age of 40 apply to the 10 family medicine units in Izmir, Turkey each month. At least 14% of these people (DM prevalence is accepted about 14%) are expected to be eligible for inclusion criteria. 3000 individuals will be evaluated in terms of inclusion and exclusion criteria. Thus, the expected sample size will be reached.

Excluded and refused to participate: Selected participants after being assessed for eligibility will be asked about voluntariness for intervention. They will be taken informed consent. Then the participants will be taken to randomization.

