• Over age 40 • Volunteer • Computer and Internet literacy • DM diagnosed or having at least one of diagnostic criteria. These criteria; • HbA1c ≥ 6.5 • FPG ≥ 126 mg / dl • 2-h postprandial glucose ≥200 mg / dl • Any time postprandial glucose ≥200 mg / dl • Diabetes symptoms	• Having communication problems • Type 1 diabetes • MODY type DM • Psychotic disorders • Dementia

### Stage 2

In the second stage, the health data of 3000 participants will be evaluated to determine the effectiveness of CDSMS in screening. Participants who use medicine for DM treatment will be excluded from data analysis when measuring the effectiveness of the system in screening.

Patients who applied to primary health care services for any reason and screened within the scope of periodic health care for diabetes, having at least one measurement of FPG (Fasting Plasma Glucose), HbA1C or PPG (Postprandial Plasma Glucose) in last six months will be participants of stage 2. Participants determined in second phase will be evaluated in terms of inclusion and exclusion criteria. Eligible and volunteer participants will take part in the trial. Inclusion and exclusion criteria for randomized controlled trial are listed below in Table 1.

Patients who were diagnosed with DM among 3000 participants (new diagnosis, former diagnosis, medicine users, non-medicine users) will form the population of the randomized controlled trial. The sample size evaluated by significance level *p* = 0.05, 80% power, 25% prevalence (controlled diabetes) and odds ratio 2 will be included to experimental study. Because in RCT studies lost to follow up is approximately 15.0%, this amount is taken into account for determining the sample size. The sample contains 439 patients with 110 interventions and 329 control groups. The ratio of intervention to non-intervention (controls) is 1:3. About 3000 people over age 40 apply to the 10 primary health care units (In the city of Izmir in Turkey) in a month. For reaching expected number of samples, at least %14 of patients are thought to be eligible for inclusion criteria. (assuming DM prevalence approximately 14%).

Diabetes symptoms aforementioned in Table 1 are classical symptoms of polyuria, polydipsia, polyphagia or loss of appetite, weakness, fatigue, dry mouth, nocturia. Less common symptoms are blurred vision, unexplained weight loss, persistent infections, recurrent yeast infections and itching [10].

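### The stated yield of at least 14% from 3000 people secures only 420, so the claim that the sample of 439 will be reached does not follow

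*Protocol article*

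**What the plan says.** All references are to the protocol article.

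- **Target.** Participants and sample size, Stage 2: "The sample contains 439 patients with 110 interventions and 329 control groups". The inputs are "significance level *p* = 0.05, 80% power, 25% prevalence (controlled diabetes) and odds ratio 2", and "The ratio of intervention to non-intervention (controls) is 1:3".
- **Loss.** Same section: "Because in RCT studies lost to follow up is approximately 15.0%, this amount is taken into account for determining the sample size". Neither the formula nor the number before the loss allowance is printed.
- **Source of trial patients.** The same section draws the trial population from "Patients who were diagnosed with DM among 3000 participants".
- **Yield.** Enrollment: "At least 14% of these people (DM prevalence is accepted about 14%) are expected to be eligible for inclusion criteria". Participants and sample size makes the same statement with the same reason. No other yield appears.
- **Conclusion drawn.** Enrollment: "3000 individuals will be evaluated in terms of inclusion and exclusion criteria. Thus, the expected sample size will be reached".
- **Consent step.** Enrollment then says "Selected participants after being assessed for eligibility will be asked about voluntariness for intervention", with informed consent and randomisation to follow.

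**The concern.** The conclusion is presented as a consequence of the figures before it, and those figures do not produce it. The minimum yield applied to 3000 falls below 439 before anyone has declined.

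The 14% is also a prevalence standing in for an eligibility rate. Having diabetes is only one condition in Table 1. The table also requires computer and internet literacy and willingness to take part, and it excludes type 1 and MODY diabetes, dementia, psychotic disorders and communication problems. Stage 2 further requires a glucose or HbA1c result within six months. The Enrollment section foresees refusals but allots no number to them.

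If 3000 is taken as the full pool for the trial, nothing in the article says what happens should that pool yield fewer than 439. Any shortfall would lower a power that, on the stated inputs, already sits slightly under 80% once the 15% loss has occurred.

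**Working it through.** **Recruitment, from printed figures only**

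1. Minimum yield: 3000 × 0.14 = 420.
2. Gap to target: 439 − 420 = 19, and 19/439 = 4.3%.
3. Fraction needed: 439/3000 = 14.63%, eligible and consenting together.
4. Number to assess at 14% with everyone consenting: 439/0.14 = 3135.7, so 3136.
5. With refusals (the consent rates are assumptions, since the article gives none): at 90%, 439/(0.14 × 0.90) = 3484.1, so 3485; at 80%, 439/(0.14 × 0.80) = 3919.6, so 3920.
6. Chance variation: if exactly 14% were the true rate and all consented, the binomial probability of 439 or more from 3000 is about 0.17.

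**Reproducing 439**

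Inputs: alpha 0.05 (taken as two-sided, because sidedness is not stated), 80% power, 25% controlled in the control arm, odds ratio 2, ratio 1:3.

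1. Intervention rate: odds = 2 × 0.25/0.75 = 0.667, so p = 0.667/1.667 = 0.40. The difference is 0.15.
2. Pooled rate: (0.40 + 3 × 0.25)/4 = 0.2875.
3. Kelsey formula: n(intervention) = (1.960 + 0.842)² × 0.2875 × 0.7125 × (4/3)/0.15² = 95.3, so 96. Control: 3 × 95.28 = 285.8, so 286. Total 382.
4. Multiplying by 1.15: 96 × 1.15 = 110.4 and 286 × 1.15 = 328.9, total 439.3. This matches 110, 329 and 439.
5. An allowance that offsets a 15% loss divides by 0.85: 382/0.85 = 449.4, so 450.
6. What 439 leaves: 439 × 0.85 = 373.15, about 373, which is 9 below 382.

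**Power after 15% loss (two-sided 0.05, 25% v 40%, 1:3, patients treated as independent)**

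| Randomised | Evaluable | Fleiss | Kelsey |
|---|---|---|---|
| 439 | 373 | 78.0% | 79.2% |
| 420 | 357 | 76.2% | 77.4% |

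For reference, 382 evaluable gives 80.1% by Kelsey.

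**Sensitivity to the formula.** Other two-sided variants with 25% in the control arm need more evaluable patients: log odds ratio 389, Fleiss 394–396, arcsine 404, unpooled 423, Fleiss with continuity correction 428–432. So 373 is short under each of them. A one-sided test would need only 312 (348 with continuity correction). Those totals inflate to 368 and 410 when divided by 0.85, or 359 and 401 when multiplied by 1.15, so they do not lead to 439.

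**The case against.** The 14% is stated as a minimum, and 3000 is an approximate figure. A true yield of 14.63% is compatible with at least 14%, so a reader who infers that the trial must close short of 439 has turned a floor into a ceiling. This objection stands.

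The figure of 3000 also has three uses: the size of the screening evaluation, one month's attendance at the ten units, and the pool for the trial. No rule stops recruitment at 3000. At 14% and full take-up, 136 more people would do, about 5% of a month's flow. That stands too, and it makes the problem cheap to cure. It does not rescue the stated inference, which rests on assessing 3000.

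Willingness and computer literacy are listed as inclusion criteria in Table 1, so an eligible share of 14% could be read as already net of both. But the article justifies the 14% by prevalence alone and asks about willingness after eligibility has been assessed. This is an ambiguity to clear up, not proof of a further loss of known size.

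A reader might apply the 13.7% quoted in the Background to widen the gap. That figure describes the Turkish population. The trial pool is attendees over 40 with a recent glucose or HbA1c result, and nothing bounds that pool at 13.7%.

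On the loss allowance, 382 is a back-calculation. A second route also reaches 439 and divides correctly by 0.85: unpooled variance with 25% in the small arm and 40% in the large one gives 93.3 + 279.9 = 373.3 before rounding of the parts, and 373.3/0.85 = 439.1. It puts the better outcome in the control arm, so it is an unlikely basis. It does mean that the printed figures alone do not prove that 1.15 was used as a multiplier.

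**Conclusion.** The recruitment point holds on printed figures. The plan's own minimum yields 420, not 439, before the consent step, so the statement that the target will be reached is unsupported. The gap at that minimum is 19 patients, worth about 2 points of power (76–77% instead of 78–79%). Refusals would widen it by an amount the article gives no means to quantify. Much larger power losses can be produced by assuming low take-up, but such figures would describe the assumption and not this plan.

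The loss allowance is a minor, inferred note. It rests on a two-sided test and on the Kelsey formula being the one used. The power of 78–79% at 439 depends less on that inference: it follows from the stated inputs and 15% loss by the Fleiss and Kelsey formulas, however 439 was obtained. The shortfall from 80% is about 1 to 2 points, and it should not be read as a serious failure of power. These figures make no allowance for clustering by physician.

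**What to change.** 1. Keep 3000 as the size of the screening evaluation, and state separately that recruitment to the randomised trial continues until 439 are randomised.
2. Replace the sentence claiming that the sample will be reached with the expected number to assess: about 3140 at 14% with full take-up, and about 3500–3900 if 90–80% consent, labelled as an assumption. Say whether the 14% is diabetes prevalence or the share meeting all Table 1 criteria, and whether it includes consent.
3. Print the sample size formula, the sidedness and the number before the loss allowance. Restate power at 439 with 15% loss as about 78–79%. If the sponsor prefers to hold 80% under the Kelsey formula, the alternative is 450 (113 + 337), which needs about 3215 assessed at 14% with full take-up.

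The cost is protocol wording, a slightly less favourable power statement and a somewhat longer screening window. At about 3000 attendees a month, 3136 is 136 more people (about 5% of a month) and 3920 is 920 more (about 31% of a month).

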#### Allocation

Eligible participants will be assigned to intervention and control groups with simple randomization using a computerized random number generator for assignment into two groups. 110 patients will be allocated to the intervention group and 329 patients to the control group. Three physicians will treat and monitor intervention group using the CDSMS. In the control group, seven physicians will treat and monitor without using CDSMS.

Researchers will determine the random allocation sequence and make lists of sequence. These lists will be given to the nurses of the family medicine center. The nurses will assess the patient according to eligibility criteria and allocate eligible patients to either intervention or control groups depending on the lists.

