### Design and settings

The study design is a parallel single blind randomized controlled trial**.** The research will be conducted in Dokuz Eylül University (DEU) Family Medicine Outpatient Clinic and selected family medicine units in İzmir. DEU Hospital is a university hospital in Izmir, the third largest city in Turkey. The family medicine outpatient clinic provides primary healthcare services to outpatients in the DEU department of family medicine.

The family medicine units which provide primary health care are located widely in Izmir. There are 972 family medicine units in Izmir metropolis. They serve under Turkish Ministry of Health. In Turkey, electronic health record systems are used for the health care services of the family medicine units. These systems mainly records preventive health care services, disease diagnoses and drug related data. Because there is not a governmental obligation, these systems have not any evidence-based sets.

In this study, validation of the developed CDSMS will be done in two stages. In first stage, the understandability and usability and adequacy of the system will be tested. Necessary adjustments will be made in the program in accordance with feedbacks taken from physicians and patients who use the application.

In the second stage, effectiveness of CDSMS will be evaluated by conducting a parallel single blind randomized controlled trial. Consort schema [37] of the RCT is in Fig. 1.

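### Simple randomisation does not fix the stated 110/329 arm sizes or balance recruiting units; a centrally held 1:3 list blocked within unit would come close on both.

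*Protocol article*

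**What the plan says.** The Abstract (Methods) and the Allocation section both name simple randomisation. Allocation says that eligible patients will be "assigned to intervention and control groups with simple randomization using a computerized random number generator for assignment into two groups" and goes straight on to state that "110 patients will be allocated to the intervention group and 329 patients to the control group". The randomisation sentence gives no 1:3 weight. The ratio appears only in the Stage 2 text of Participants and sample size: "The ratio of intervention to non-intervention (controls) is 1:3". The same paragraph gives the total: "The sample contains 439 patients with 110 interventions and 329 control groups".

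No blocking, stratification or other restriction is mentioned. The setting is the "Dokuz Eylül University (DEU) Family Medicine Outpatient Clinic and selected family medicine units in İzmir", and ten primary care units are to supply the patients. Allocation also says that researchers prepare the lists and hand them to nurses, who both judge eligibility and assign the arm.

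**The concern.** Under simple randomisation each patient is an independent draw, so the arm totals are outcomes of the method and cannot be set in advance. If 110 and 329 are meant as binding, a simple sequence would usually have to be cut short or overridden to reach them, and the last assignments would become predictable to whoever holds the list. Here that is the nurse who decides on eligibility.

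The draws are also not tied to the recruiting unit. A university clinic and Ministry of Health units may differ in case mix and prior care, so recruiting unit is a natural stratum, and simple randomisation does nothing to even it out. At stake are the size of the smaller arm, some precision, and concealment of the allocation.

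**Working it through.** **Inputs.** Total 439, arms 110/329, ratio 1:3, and "80% power, 25% prevalence (controlled diabetes) and odds ratio 2" with significance level 0.05 and loss of about 15% (Participants and sample size, Stage 2). Ten units (same section). Assumptions: a two-sided test, and equal units of 439/10, or about 44 patients.

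**1. Reproducing the plan's figure.** The odds of control at 25% are 1/3. Doubled they are 2/3, which gives 40% in the intervention arm. With a pooled variance, the average proportion is (0.40 + 3 × 0.25)/4 = 0.2875, and

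n(intervention) = 7.849 × 0.2875 × 0.7125 × (4/3) / 0.15² = 95.3, rounded up to 96.

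Three times 95.3 gives 286 controls, a total of 382, and 382 × 1.15 = 439. Split 1:3, this is 110/329. The stated sample therefore reproduces and is not in question here.

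**2. Arm size under simple 1:3 draws.** The intervention count is Binomial(439, 0.25).
- Mean 439 × 0.25 = 109.75; SD √(439 × 0.25 × 0.75) = 9.07.
- 95% range 92 to 128.
- P(exactly 110) = 0.044.
- P(within 10 of 110) = 0.75.

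**3. Power across that range.** Two-sided test of 40% against 25%, with pooled variance under the null and separate variances under the alternative. After 15% loss, 110/329 becomes 93.5/279.65. The standard errors are then 0.0541 (null) and 0.0569 (alternative), and power = Φ[(0.15 − 1.96 × 0.0541)/0.0569] = 78.0%. The other rows use the same formula.

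| Intervention / control | Power, all 439 | Power after 15% loss |
|---|---|---|
| 92 / 347 | 79.7% | 73.3% |
| 110 / 329 | 84.1% | 78.0% |
| 128 / 311 | 87.1% | 81.5% |

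**4. Balance by recruiting unit.** With 44 patients in a unit, the intervention count is Binomial(44, 0.25): mean 11, 95% range 6 to 17 (14% to 39% of the unit). The chance of falling outside that range (5 or fewer, or 18 or more) is 0.0363 per unit. For at least one of ten units it is 1 − (1 − 0.0363)^10 = 31%.

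**5. What a blocked list would give.** Simulated 1:3 permuted blocks within ten units of equal expected size, 439 patients, with incomplete last blocks allowed.

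| Block size | 95% range, intervention arm | Largest departure from 1:3 in a unit |
|---|---|---|
| 4 | 107 to 112 | 0.75 patients |
| 8 | 106 to 113 | 1.5 patients |
| 4 and 8 at random | 107 to 113 | 1.5 patients |

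Exactly 110 comes up in about 32% of runs with blocks of 4 and about 25% with mixed blocks, so blocking comes close to 110/329 without guaranteeing it.

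**The case against.** Planned arm sizes are routinely stated as round targets, and a 1:3-weighted simple list does average 110. The term is also used loosely: a list of 439 prepared in advance with 110 intervention places would give the stated split exactly. This is fair. A reader might infer that the method cannot deliver 110/329, or that nurses will have to override the sequence; the document supports neither. What stands is that the method as named does not fix the totals stated beside it.

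A reader might also take the two-group wording to mean an unweighted generator. That would give 199 to 240 intervention patients and put 110 out of reach. The stated 1:3 ratio makes this unlikely, although the randomisation sentence should carry the weight.

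It is tempting to call unit imbalance confounding. It is not: under randomisation, unit of origin is balanced in expectation and the standard error covers the chance variation. Nor is the 31% a sign of a defect, since ten separate 95% ranges would be expected to produce about that much. The planned primary-outcome model, with group, period and their interaction, also takes account of baseline level. Stratifying by unit is therefore an improvement in precision and not the repair of a bias.

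Finally, the larger imbalance is structural. Allocation assigns three physicians to the intervention arm only and seven to the control arm only, which ties arm to treating physician. Blocking by recruiting unit leaves that untouched. This objection stands in full and limits what the fix can claim.

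**Conclusion.** The point holds as a minor inconsistency with a better method available. Simple randomisation and fixed arms of 110 and 329 do not belong together as written. Under 1:3 draws the intervention arm would usually lie between 92 and 128, which moves power after 15% loss by about 5 points down or 4 points up from 78%. Imbalance by unit (6 to 17 of 44) is a loss of precision only. These figures assume a 1:3 weight, a two-sided test and ten equal units; unequal units would change the per-unit range.

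The gain from a blocked, centrally held list is limited to arm size, recruiting-unit balance and concealment. It should not be read as answering the three-against-seven physician split, which has to be reconciled separately with patient-level randomisation.

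**What to change.** In the Abstract and in Allocation, replace simple randomisation with a computer-generated 1:3 list in permuted blocks of randomly varying size (4 and 8), stratified by the unit where the patient is recruited. Hold the list centrally and release it one patient at a time, after eligibility and consent are recorded, so that the nurses who assess eligibility no longer hold it. Include recruiting unit in the outcome model. Describe 110/329 as planned sizes, with about 107 to 113 intervention patients expected from the blocked list.

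The cost is a change of wording, a different list-generation program and a central release procedure. Blocks are somewhat more predictable than simple draws where the arm is visible; varying the block size and releasing centrally limit this. The physician split needs its own correction, and this change should not be presented as covering it.

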**Methods:**

The CDSMS will be based on evidence-based guidelines for DM disease. A web and mobile-based application will be developed in which the physician will remotely monitor patient data through mobile applications in real time.

The developed CDSMS will be tested in two stages. In the first stage, the usability, understandability, and adequacy of the application will be determined. Five primary care physicians will use the developed application for at least 16 DM patients. Necessary improvements will be made according to physician feedback. In the second phase, a parallel, single-blind, randomized controlled trial will be implemented. DM diagnosed patients will be recruited for the CDSMS trial by their primary care physicians. Ten physicians and their 439 patients will be involved in the study. Eligible participants will be assigned to intervention and control groups with simple randomization. The significance level will be accepted as *p* < 0.05. In the intervention group, the system will make recommendations on patient monitoring, diagnosis, and treatment. These recommendations will be implemented at the physician’s discretion. Patients in the control group will be treated by physicians according to current DM treatment standards. Patients in both groups will be monitored for 6 months. Patient data will be compared between 0th and 6th month of the study. . Clinical and laboratory outcomes will be assessed in person while others will be self-assessed online.

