Patient therapy evaluations	Patients’ satisfaction with therapy	The Patient Assessment of Chronic Illness Care-Patient Form [44, 45]
User program evaluations	Users’ program usage, perceived utility and acceptability, ease of use, user interface, and satisfaction with program	Web Site Usability Scale [38] Feedback form

Participants in the intervention group will be given screening, diagnosis, treatment and monitoring services by the physicians using CDSMS for six months. These patients will be monitored in the framework of the protocols. The control group patients will receive services from physicians as they have done before without further intervention. All tests and scales implemented on screening and baseline will be repeated at the end of six months. By comparing the two groups, the effectiveness of the study will be measured. The measures and scales used at screening (enrollment), baseline, monthly, quarterly and at the end of intervention are summarized in Table 3.

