### Statistical analysis

Statistical analysis will be performed using SPSS software. As stated in the method section, the system will be tested in two stages.

### Stage 1

For the first stage, the comments in the feedback forms will be used for revisions of program. Descriptive analyzes will be done for web site usability test results.

### Stage 2

At the end of the intervention, independent samples t-tests will be performed to measure the difference between the intervention and control groups. On both groups, one-sample t-test will be performed to measure the difference between baseline and post intervention in the same group.

Each of the dependent measures of primary outcomes will be analyzed using a generalized linear mixed model involving a single between Group factor (Treatment vs. Control), a single within Period factor (enrollment vs. end of 6 months), and interaction between Group and Period factor. Categorical data of both control and intervention groups will be analyzed together using logistic regression. The rates of controlled and uncontrolled diabetes patients will be determined.

An intention-to-treat analysis will be performed. The analysis will include all individuals’ data. In the analysis, patients will be compared regardless of patient compliance, crossover to other treatments, or withdrawal from the study.

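### Each arm is treated by its own physicians (three versus seven), yet the sample size and the listed tests treat the 439 patients as independent

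*Protocol article*

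**What the plan says.** Protocol article, Allocation: eligible participants are assigned by simple randomisation, 110 to intervention and 329 to control. The same section continues: "Three physicians will treat and monitor intervention group using the CDSMS. In the control group, seven physicians will treat and monitor without using CDSMS". No physician is described as treating in both arms, and the article does not say how the three were chosen.

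Participants and sample size, Stage 2: the size rests on a 0.05 significance level and "80% power, 25% prevalence (controlled diabetes) and odds ratio 2", a 1:3 ratio, and an allowance for attrition: "Because in RCT studies lost to follow up is approximately 15.0%, this amount is taken into account for determining the sample size". No ICC, cluster size or design effect is given.

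Statistical analysis, Stage 2: independent-samples t-tests between groups, logistic regression for categorical data, and for the primary outcomes a "generalized linear mixed model involving a single between Group factor (Treatment vs. Control"), with Period and Group x Period as the other listed terms. Physician is not among them.

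Two further statements bear on who treats whom. The Abstract says "Ten physicians and their 439 patients will be involved in the study". Measures says "The control group patients will receive services from physicians as they have done before without further intervention".

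**The concern.** The intervention works through the physician: the system makes a suggestion and the physician decides. Patients of one physician share that physician's habits, so their outcomes are likely to be correlated. With three physicians in one arm and seven others in the other, the contrast between arms is also a contrast between two small sets of physicians. Randomising patients can balance who the patients are. It cannot balance how the physicians treat.

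Two things are at stake. A difference between these physicians can be read as an effect of the system. And a test that counts 439 independent patients uses a standard error that is too small, so a significant result is easier to obtain by chance than 5% implies, and the 80% power is not the power of a valid test.

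**Working it through.** **1. Reproduce 439.** Inputs from Participants and sample size: control rate 0.25; odds ratio 2, so odds 2 x 0.25/0.75 = 0.667 and intervention rate 0.40; ratio 1:3; 80% power. Sidedness is not stated; two-sided 5% is used here.

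Pooled rate = (0.40 + 3 x 0.25)/4 = 0.2875.

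n1 = (1.960 + 0.842)² x 0.2875 x 0.7125 x (4/3) / 0.15² = 95.28.

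Times 1.15 for loss: 109.6, that is 110; three times that is 328.7, that is 329; total 439. The match is exact. The formula is for independent patients, with no room for a design effect.

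**2. Cluster sizes.** Taking 15% loss from 110 and 329 leaves 93.5 and 279.65 evaluable patients. Per physician: 93.5/3 = 31.2 and 279.65/7 = 39.9.

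**3. Type I error of a patient-level test.** The ICC is an assumption and is shown as a range. It refers to the outcome tested; for Group x Period it is the ICC of six-month change.

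- Design effect per arm: d = 1 + (m - 1) x ICC.
- Variance ratio: R = (d1/93.5 + d2/279.65) / (1/93.5 + 1/279.65).
- Actual error: 2 x [1 - Φ(1.96/√R)].

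Example, ICC 0.02: d1 = 1.60, d2 = 1.78, R = 1.65, √R = 1.28, 1.96/1.28 = 1.53, error about 12.7%.

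**4. Power of a test that respects physicians.** Ten physician means give 10 - 2 = 8 degrees of freedom.

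SE = √(0.40 x 0.60 x d1/93.5 + 0.25 x 0.75 x d2/279.65). Power comes from the noncentral t with noncentrality 0.15/SE.

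Example, ICC 0.02: SE = 0.073, noncentrality 2.06, power 44%.

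| Assumed ICC | d1 / d2 | Type I error, patient-level test | Power, 8 df, after loss | Power, 8 df, all 110/329 |
|---|---|---|---|---|
| 0 | 1.00 / 1.00 | 5.0% | 64% | 71% |
| 0.01 | 1.30 / 1.39 | 8.9% | 52% | 57% |
| 0.02 | 1.60 / 1.78 | 12.7% | 44% | 48% |
| 0.05 | 2.51 / 2.95 | 22.6% | 30% | 32% |

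A beta-binomial simulation at 110/329 (20,000 runs per setting) gave type I errors of 9.8, 14.0 and 25.0% at ICC 0.01, 0.02 and 0.05. The formula gives 9.6, 14.0 and 25.1% at those sizes.

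**5. Where the power goes.** After loss and with ICC 0, the same standard error with a normal test gives 75% (78% with the pooled-variance formula). Moving to 8 df gives 64%. Only the fall from 64% to 52, 44 or 30% is due to ICC.

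**6. More patients do not cure it.** With unlimited patients per physician, the variance tends to ICC x (0.24/3 + 0.1875/7). Power is then capped at about 81% for ICC 0.02 and 44% for ICC 0.05.

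**7. Who moves.** Assume ten equal caseloads and individual randomisation. About 70% of intervention patients (0.7 x 110 = 77) come from the seven control physicians and must move. About 30% of controls (0.3 x 329 = 99) come from the three intervention physicians and must move too. If nobody moves, arm equals existing physician, and the split is about 0.3 x 439 = 132 versus 307.

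**The case against.** The strongest reply has four parts.

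- **The ICC is not given and could be negligible.** At exactly 0 the patient-level 5% holds. Group x Period also removes stable differences between caseloads at baseline. Both are true, which is why a range including 0 is shown. What remains is variation between physicians in how much their patients change, and the interaction term does not remove that.
- **The mixed model's random effects are not described.** A reader might infer that every planned analysis ignores physicians. The article does not support that for the mixed model: it lists factors only, and a condensed article may leave the random part to a fuller document. The point rests on the sample size, the t-tests and the logistic regression, and on the mixed model only as far as its terms are listed.
- **Allocation is stated plainly as individual.** A reader might infer that arms are really set by each patient's existing physician, so that case-mix is biased. No section says so. The sentence in Measures can simply mean usual care, and the Abstract's wording concerns recruitment. Under individual randomisation, case-mix is balanced in expectation. What stands is that the handover between physicians is unclear, and that case-mix imbalance follows only if nobody moves.
- **The fall from 80% to 52, 44 or 30% is not all clustering.** This stands; the ICC 0 row shows the part that is not.

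**Conclusion.** The point holds. Physician is fully nested in arm by explicit text, so part of any observed effect may belong to the physicians and not to the system. The sample size ignores this, as its exact reproduction shows, and so do the stated t-tests and logistic regression. For any physician ICC above 0, the 5% level and the 80% power do not hold.

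The size depends on assumed ICCs, about 93 versus 280 evaluable patients, equal caseloads within each arm, and 40% versus 25% controlled. Over ICC 0 to 0.05, type I error of the patient-level test runs from 5 to 23%, and 8-df power from 64 to 30%.

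A reader might also infer that a physician random effect would settle the matter. It would not: with three physicians in one arm it corrects the standard error only roughly, and no model term removes the confounding.

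**What to change.** 1. **Statistical analysis, Stage 2.** Replace the independent-patient t-tests with a test of the ten physician-level mean changes (8 df), or add a physician random effect with small-sample degrees of freedom to the mixed and logistic models.
2. **Participants and sample size, Stage 2.** Replace the 80% power statement with the power for three versus seven physicians over a stated ICC range that includes 0.
3. **Allocation.** Reconcile this section with the Abstract and Measures on the unit of allocation and on whether patients change physician. Choose the three physicians who use the system by a random draw. State as a limitation that the effect remains partly confounded with physician.

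Cost: items 1 and 2 are changes of wording and analysis, and the stated power becomes less favourable. Item 3 needs one random draw and a decision. If patients stay with their own physician, arm sizes will be about 30:70 (132/307 with equal caseloads) and not 110/329. More physicians per arm would weaken the confounding further, but that is a larger design change.
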